### Outcome measures

The variable of the main result will be clinical cure at 14 days, defined as absence of fever, resolution or improvement of cough, improvement of general wellbeing and normal respiratory auscultation or reduction of crackles indicating that no other antimicrobial treatment is necessary. Any clinical result other than the anterior will be considered as treatment failure. Variables of secondary results will be efficacy at day 30 after the initiation of antibiotic treatment, radiological resolution or improvement one month after the initiation of the treatment, complete clinical resolution at day 14 defined as the total resolution of acute symptoms and signs related to the infection, the presence of adverse events which may appear during the treatment, and compliance with treatment administered. The radiologists responsible for diagnosing pneumonia and confirming the radiological cure will be blind to the clinical data and the treatment administered.

### Ascertainment of visits

On fulfilling the inclusion criteria the nature of the study will be explained to the patient and informed consent will be requested. All the eligible patients should have a chest X-ray (posteroanterior and lateral projection) demonstrating pneumonic infection. The study scheme and the visit program will be explained to the patient (Table 1). The patients will be randomised to one of the 2 treatment groups and the medication given. The first dose of the drug will be administered in the presence of the investigator. They will be dispensed the drugs for ten days.

**Table 1 T1:** Variables to be collected during the clinical trial

	**Visit 1**	**Visit 2**	**Visit 3**	**Visit 4**
	**Day 0**	**Day 3**	**Day 14**	**Day 30**
**Medical history and examination**	x	x	x	x
**Pulse oximeter determination**	x	x	x	x
**Chest X-ray**	x			x
**Informed consent form**	x			
**Randomisation**	x			
**Evaluation of clinical evolution**		x	x	x
**Assessment of adverse events**		x	x	x
**Review of compliance**		x	x	

At the first follow-up visit, scheduled at day 3, a worsening of the clinical situation of the patient will be evaluated to determine whether a change in the antibiotic treatment is necessary. Likewise, compliance and possible secondary effects of the treatment will be evaluated. At the second follow-up visit, at day 14, the clinical evolution of the signs and symptoms will be evaluated and the need to change the antibiotic treatment in the case of worsening in the clinical manifestations will be determined. Likewise, compliance and possible secondary effects of the treatment will be evaluated. The last follow-up visit, scheduled at day 30, the clinical outcome of the signs and symptoms of the pneumonia will be evaluated and a new chest X-ray will be performed (posteroanterior and lateral projection) to confirm radiological resolution of the pneumonia. The medication will be discontinued in the case of clinical failure in follow-up visits 2 and 3 or in the case of significant adverse events.

The variables will be registered in an electronic case report form designed by the Hospital Universitari Vall d’Hebron (Barcelona, Spain). The variables considered in this trial will be sociodemographic (birth date, gender, race) and toxic habits (smoking and drinking behaviours), present medical history (presence and duration of signs and symptoms: fever, cough, expectoration, sputum purulence, diarrhoea, malaise, muscular aches, joint aches, thoracic pain, dyspnoea, respiratory auscultation; and details of any history of high blood pressure, type 2 diabetes mellitus or hypercholesterolemia), physical examination (axillary temperature, resting pulse, respiratory rate, blood pressure measurements, oxygen saturation, and auscultation abnormalities) and X-ray findings.

### Sample size

The objective of the study is to demonstrate that penicillin V is not inferior to amoxicillin. Considering a success rate of 85% for the group treated with amoxicillin [20,21] a total of 105 patients will be required in each treatment group (total of 210) to detect a non-inferiority margin of 15% at maximum between the two treatments with a minimum power of 80% considering an alpha error of 2.5% for a unilateral hypothesis and maximum possible losses of 15%.

### Statistical analyses

The intention-to-treat (ITT) population will include all randomised patients receiving at least one dose of study drug and the per-protocol (PP) population will include patients receiving no systemic antimicrobial agents other than the study drug for at least three days in the case of clinical failure or ≥80% of study medication in the case of cure, with adequate assessment of compliance and absence of major protocol violations.

To evaluate the comparability of the groups the two groups will be analysed with variables expressed as means and standard deviations for the case of quantitative variables and with proportions in the case of qualitative variables. The variable of the principle result, clinical cure, will be expressed as percentages and the comparison of percentages in the two treatment groups will be analysed using the Chi-square test. Logistic regression will be performed for the analysis of the predictive factors of cure or not, with calculation of the odds ratio for each of the variables analysed and multiadjustment for each of the factors of the study with confidence intervals of 95%. Variables with a p<0.20 on bivariant analysis will be included in the analysis. A p value < 0.05 will be considered statistically significant.

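### The primary comparison of day-14 cure makes no use of the severity measures recorded at day 0: a valid analysis, but a modest efficiency may be missed

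*Protocol article*

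**What the plan says.** **Primary outcome.** Under Outcome measures, cure at day 14 requires "absence of fever, resolution or improvement of cough, improvement of general wellbeing and normal respiratory auscultation or reduction of crackles", such that no further antimicrobial is needed.

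**Primary comparison.** Under Statistical analyses, cure is expressed as percentages and "the comparison of percentages in the two treatment groups will be analysed using the Chi-square test". No covariate is named.

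**Baseline data.** Under Ascertainment of visits, Table 1 schedules history, examination and pulse oximetry at day 0. The variables listed there include presence and duration of symptoms such as fever, cough and malaise, and "physical examination (axillary temperature, resting pulse, respiratory rate, blood pressure measurements, oxygen saturation, and auscultation abnormalities) and X-ray findings". Birth date is also collected, so age is available.

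**Planned regression.** Statistical analyses also plans a logistic regression to look for factors that predict cure. Variables enter if p<0.20 in bivariate analysis, and results are odds ratios with 95% intervals.

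**Sizing.** Under Sample size, the inputs are "Considering a success rate of 85% for the group treated with amoxicillin", a 15-point margin, one-sided alpha of 2.5%, power stated as a minimum of 80%, losses stated as at most 15%, and 105 patients per arm.

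**The concern.** The margin is a difference in percentages, so the conclusion depends on how precisely that difference is estimated. If day-0 severity predicts day-14 cure, adjusting for it narrows the interval and reduces the influence of a chance difference in severity between two arms of about 89. The data for this will already be on the case report form.

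The plan does foresee adjustment, but in a form that cannot serve the non-inferiority question. The logistic model is a search for predictors, its covariates are chosen after the data are seen, and an odds ratio cannot be read against a 15-point margin. What is at stake is a few points of power at no cost in patients. The validity of the result is not at stake.

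**Working it through.** **Inputs from the Protocol article (Sample size):** amoxicillin cure 85%; margin 0.15; one-sided alpha 2.5%; power at least 80%; losses at most 15%; 105 per arm.

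**Assumptions not in the documents:** true penicillin V cure of 85% (this reproduces the stated size), and the correlation rho between baseline severity and cure.

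**Step 1: reproduce the plan's figure.** The unadjusted calculation needs 89 evaluable per arm. Allowing for losses, 89/0.85 = 104.7, rounded up to 105. This matches the plan.

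**Step 2: unadjusted power at 89 per arm.**
- SE = sqrt(2 × 0.85 × 0.15 / 89) = 0.0535
- z = 0.15 / 0.0535 = 2.80
- Power = Φ(2.80 − 1.96) = 80.0%
- 95% half-width = 1.96 × 0.0535 = 10.5 points

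**Step 3: unadjusted power with fewer losses.** With no losses (105 per arm) the same formula gives 86.1%. With 10% losses (94.5 per arm) it gives about 82%, and with 5% (99.75 per arm) about 84%.

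**Step 4: adjusted power at 89 per arm.** Adjustment multiplies the variance by (1 − rho²), so power = Φ(2.80 / sqrt(1 − rho²) − 1.96) and half-width = 10.5 × sqrt(1 − rho²).

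| Assumed rho | Power | 95% half-width (points) |
|---|---|---|
| 0 | 80.0% | 10.5 |
| 0.2 | 81.6% | 10.3 |
| 0.3 | 83.6% | 10.0 |
| 0.4 | 86.4% | 9.6 |

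A gain of 5 points needs rho of about 0.355.

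**Step 5: simulation with one severity score** (linear model with treatment-by-covariate term and robust standard errors, 8,000 trials per scenario). Unadjusted to adjusted power:
- odds ratio 2 per SD: 80.0% to 81.7%
- odds ratio 2.5 per SD: 79.5% to 82.7%
- odds ratio 3 per SD: 80.7% to 85.0%

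An odds ratio of 2 per SD corresponds to rho of about 0.24, and 3 per SD to about 0.37. One-sided error at a true 15-point deficit was about 2.4% to 2.9% with or without adjustment (5,000 trials).

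**Step 6: separate simulation with four covariates** (logistic model standardised to a risk difference, 89 per arm, 4,000 trials per setting).

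| Share of outcome variance explained | Unadjusted power | Adjusted power |
|---|---|---|
| 0 | 80.3% | 79.8% |
| 0.02 | 79.9% | 80.6% |
| 0.06 | 80.1% | 82.0% |
| 0.12 | 80.0% | 84.7% |
| 0.20 | 80.6% | 88.0% |

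Useless covariates cost about half a point. The last row corresponds to rho = sqrt(0.20) = 0.45, which is strong prognosis.

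**Step 7: room for covariates.** Expected failures are 2 × 89 × 0.15 = 26.7, or about 27. That allows only a few.

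**The case against.** The strongest reply is that nothing here is wrong. The trial is sized for an unadjusted comparison and plans one, and Step 1 shows that the two agree. Covariate sets are also often left to an analysis plan, and none is shown. The first part stands: this is an improvement, not a defect. The second stands only in part, because the article does not leave the primary comparison open. It names an unadjusted test, which a later analysis plan would have to override.

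Three stronger readings are tempting, and the documents support none of them.

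- **Precision is certainly being thrown away.** No section says that day-0 values predict day-14 cure. Being a component of the outcome does not make the baseline value prognostic: cough, wellbeing and auscultation can each be satisfied by improvement, which a sicker patient can also achieve. Patient selection narrows the range further by excluding, among others, temperature above 40°C, saturation below 92% and infiltrate in more than one lobe.
- **The trial has exactly 80% power and no reserve.** The article gives 80% as a minimum, at maximum losses. Step 3 shows about 86% with none lost. The intention-to-treat set takes in every randomised patient with at least one dose, so its size could be nearer 105 than 89 per arm.
- **A chance imbalance would invalidate the raw result.** Variation from randomisation is already in the unadjusted standard error, and simulated error rates were similar either way. Adjustment reduces imbalance only on the chosen covariates.

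It can also be said that the larger question in the same sentence is separate: a Chi-square test judged at p<0.05 tests equality and does not address the 15-point margin. That is fair. Adjustment is useful only once an interval for the difference is the basis of the conclusion, so the fix below specifies one.

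**Conclusion.** The point holds as a modest missed efficiency. The primary comparison is fixed as unadjusted, severity measures exist at day 0, and the planned regression cannot supply an adjusted difference for the margin. The unadjusted analysis remains valid, reaches the stated minimum power at 89 evaluable per arm, and the 105 per arm is correct for it.

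The size depends on an assumption. For rho from 0 to 0.4, power at 89 per arm runs from 80% to 86%. Given the eligibility limits and the improvement-based components of cure, about 0 to 4 points is the likely gain, against about half a point lost if the covariates carry no information. All figures assume 85% cure in both arms. Confidence that the gain would be material is low, because the documents give no figure for prognostic strength.

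**What to change.** In Statistical analyses:

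1. Name two or three day-0 covariates before unblinding, for example axillary temperature, oxygen saturation and age. Do not choose them by the p<0.20 screen.
2. Make the primary estimate the covariate-adjusted risk difference in day-14 cure, from a logistic model standardised to the risk-difference scale or a linear model with robust standard errors.
3. Compare its two-sided 95% interval with the 15-point margin, which corresponds to the stated one-sided 2.5%.
4. Keep the unadjusted difference with its interval as a supporting analysis, and leave the logistic regression as an exploration of predictors.

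The cost is a few sentences and slightly more analysis work, with no new data or patients and no change to the sample size. With about 27 failures expected, the covariates must stay few.

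### The stated primary test, a Chi-square test at p < 0.05, tests for a difference and never uses the 15-point margin, so no stated analysis can establish non-inferiority

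*Protocol article*

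**What the plan says.** The Sample size section of the protocol article sets the aim: "The objective of the study is to demonstrate that penicillin V is not inferior to amoxicillin". It gives the design inputs as follows: "Considering a success rate of 85% for the group treated with amoxicillin", 105 patients per arm "to detect a non-inferiority margin of 15% at maximum between the two treatments", power of at least 80%, "considering an alpha error of 2.5% for a unilateral hypothesis", and losses of at most 15%. The abstract repeats these inputs, and the hypothesis under Study hypothesis and objectives is also a non-inferiority hypothesis. The endpoint is fixed under Outcome measures: "The variable of the main result will be clinical cure at 14 days".

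Under Statistical analyses, cure is to be expressed as percentages and "the comparison of percentages in the two treatment groups will be analysed using the Chi-square test". The criterion is "A p value < 0.05 will be considered statistically significant". That section does not mention the margin, the one-sided 2.5% level or a confidence interval for the difference in cure. The only confidence intervals it names belong to the odds ratios from the logistic regression of predictive factors.

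**The concern.** A Chi-square test of two percentages asks whether the cure rates differ. A non-inferiority trial asks whether penicillin V could be worse by 15 points or more. A p value of 0.05 or above leaves the second question open, because a non-significant result can go with a confidence interval that extends well beyond -15 points. A p value below 0.05 does not settle it either, because the margin plays no part in the test.

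This is more than a detail left for an analysis plan. The article names a specific primary test, and that test does not match the hypothesis, alpha and power used to size the trial. An analysis plan with a margin-based rule would have to depart from the published primary comparison. What is at stake is the main conclusion, which the Discussion links to wider use of penicillin V. The risk of misreading is practical: the abstract and the Discussion word the question as one of equal effectiveness, and a non-significant difference test is easily taken as an answer to that.

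**Working it through.** **Inputs.** From Sample size: amoxicillin cure 85%, margin 15%, one-sided alpha 2.5%, power 80%, losses 15%, 105 per arm. From Statistical analyses: Chi-square test, p < 0.05. Two assumptions are added: the margin is an absolute difference, and the sample size takes the same 85% cure in both arms. The second is not stated, but it reproduces the plan's figure.

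**1. The plan's own sample size.**

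n = (1.960 + 0.842)² × 2 × 0.85 × 0.15 / 0.15² = 88.95, so 89 evaluable per arm.

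With 15% losses: 89 / 0.85 = 104.7, so 105 per arm and 210 in total. This matches exactly.

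A two-sided difference test of 85% against 70% at 80% power would instead need 121 per arm, or 143 after losses (121 / 0.85 = 142.4). The stated power and alpha therefore belong to a margin-based comparison and not to the named test.

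**2. The named test at the margin.** Set true cure to 85% on amoxicillin and 70% on penicillin V (85 - 15).

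Power = Φ[(0.15 - 1.96 × s₀) / s₁], where s₀ = √(2 × 0.775 × 0.225 / n) and s₁ = √((0.85 × 0.15 + 0.70 × 0.30) / n).

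- n = 89: s₀ = 0.0626, s₁ = 0.0616, argument 0.443. Probability of a non-significant result: 32.9%.
- n = 105: s₀ = 0.0576, s₁ = 0.0567, argument 0.653. Probability of a non-significant result: 25.7%.

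Exact binomial enumeration, compared with the rule that the lower two-sided 95% limit must exceed -15 points:

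| Per arm | Chi-square p ≥ 0.05 | Same, Yates-corrected | Lower Wald limit above -15 |
|---|---|---|---|
| 89 | 32.7% | 38.9% | 2.6% |
| 105 | 25.0% | 31.0% | 2.6% |

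**3. One possible result.** Take 67/89 cured on penicillin V and 76/89 on amoxicillin.

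- Difference: 75.3% - 85.4% = -10.1 points.
- Chi-square: 2.88, p = 0.09, so non-significant.
- Standard error: √(0.753 × 0.247 / 89 + 0.854 × 0.146 / 89) = 0.0591.
- 95% CI: -10.1 ± 1.96 × 5.91, which is -21.7 to +1.5 points. The lower limit is below -15, so non-inferiority is not shown.

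**4. Power of the margin-based rule at 85% in both arms (exact enumeration).**

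| Per arm | Wald interval | Newcombe interval |
|---|---|---|
| 89 | 80.1% | 78.9% |
| 105 | 86.0% | 85.5% |

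**The case against.** The strongest reply is that the protocol nowhere says a p value of 0.05 or above will be taken as non-inferiority. A reader might infer such a rule from a non-inferiority aim paired with a difference test, and so conclude that the trial carries a false-success rate of a quarter to a third. The document does not support that. The rate belongs to a decision rule it never states, and must be given as conditional on that misreading. It would also be too strong to say that the trial could not answer its question: both cure percentages will be reported, and a confidence interval can be computed from them. It is equally possible to read the Chi-square sentence as descriptive, with the claim judged on the margin in Sample size.

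Those limits stand, but they do not remove the mismatch. The one test named for the primary outcome does not use the margin, and no rule for concluding non-inferiority is given.

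A second reply is that the one-third figure is the upper end for the uncorrected test, since it assumes the full 15% losses. This also stands. The intention-to-treat set keeps every randomised patient who took a dose, and any result other than cure counts as failure, so an analysis close to 105 per arm, and hence about 25%, is plausible.

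Third, the choice of interval method, the analysis set that carries the claim, and the presentation of secondary outcomes are matters a journal article may leave to a fuller document. They are not part of this point.

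**Conclusion.** The point holds. The article fixes a test of equality at p < 0.05 as the primary comparison in a trial designed, powered and sized for non-inferiority. As stated, no analysis uses the 15-point margin or the one-sided 2.5% level, so none can establish the claim. It should be corrected because it bears on the primary conclusion.

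Its size is conditional. If a non-significant result were taken as success, the chance of false success at a true 70% against 85% would be about 25% (105 per arm) to 33% (89 evaluable per arm), compared with about 2.5% under a margin-based rule. This rests on an absolute margin, 85% cure on amoxicillin and the uncorrected Chi-square test. The sample size itself is sound: it reproduces exactly as a non-inferiority calculation.

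**What to change.** Replace the Chi-square sentence under Statistical analyses with wording such as: the primary analysis is the difference in the proportion clinically cured at day 14 (penicillin V minus amoxicillin) with its two-sided 95% confidence interval; non-inferiority is concluded only if the lower limit is above -15 percentage points. A two-sided 95% interval corresponds to the one-sided 2.5% level already chosen. Any test of difference should be labelled secondary, and the p < 0.05 criterion limited to such tests. The change should be made before unblinding.

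The cost is wording only, with no new data and no more patients. If Newcombe is preferred to Wald, the text should state that power falls just short of the 80% minimum (78.9%) should the full 15% losses occur.

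### The logistic model of predictors of cure screens covariates at p<0.20 on the same 27–32 or so failures it then tests, so its odds ratios, p-values and intervals will be over-optimistic

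*Protocol article*

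**What the plan says.** The Statistical analyses section of the protocol article plans two separate analyses of clinical cure. The treatment groups are compared by a chi-square test of percentages. In addition, "Logistic regression will be performed for the analysis of the predictive factors of cure or not", with an odds ratio for each variable analysed, multiple adjustment and 95% confidence intervals. Entry to the model is decided by "Variables with a p<0.20 on bivariant analysis will be included in the analysis". The significance level is 0.05. The section names no candidate variables, sets no limit on model size, plans no shrinkage or validation, and does not call the analysis exploratory.

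The Ascertainment of visits section describes what is recorded, beginning "The variables considered in this trial will be sociodemographic (birth date, gender, race) and toxic habits (smoking and drinking behaviours" and continuing with symptoms and signs, medical history, physical examination and X-ray findings.

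The Sample size section fixes the expected number of failures: "Considering a success rate of 85% for the group treated with amoxicillin", and "a total of 105 patients will be required in each treatment group (total of 210" patients, with losses of at most 15%.

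**The concern.** The screen and the final test use the same outcomes. A variable that passes p<0.20 by chance already carries an odds ratio pushed away from 1. The final model then gives it a p-value and an interval that take no account of that selection. With many candidates and few failures the effect is large: noise variables enter, some reach p<0.05, and the fitted model seems to discriminate better than it would in new patients.

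At stake is a published list of factors said to predict cure or failure in pneumonia treated with these two antibiotics, some of which may be chance findings. The article states the rule itself, so this is a choice already made and not a detail left to an analysis plan.

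**Working it through.** **The plan's own sample size.** Inputs: cure 85% in both arms (the article gives it for amoxicillin only; equality is assumed), margin 15 points, one-sided alpha 2.5%, power 80%.

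n per arm = 2 × 0.85 × 0.15 × (1.960 + 0.842)² / 0.15² = 88.95, so 89. Allowing for 15% losses, 89 / 0.85 = 104.7, so 105 per arm and 210 in total. This matches the article.

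**Expected failures.**
- All 210 patients at 15% failure: 210 × 0.15 = 31.5.
- After 15% losses: 210 × 0.85 = 178.5 patients; 178.5 × 0.15 = 26.8.
- All losses counted as failures: 31.5 + 26.8 = 58.3.
- Penicillin V curing only 70%: 105 × 0.15 + 105 × 0.30 = 47.3, or 47.3 × 0.85 = 40.2 after losses.

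**Candidates (assumed).** Counting the variables under Ascertainment of visits: 3 sociodemographic + 2 habits + 11 symptoms and signs + 3 history + 6 examination + 1 X-ray = 26. Auscultation appears twice in that count, and symptom durations could add to it. Failures per candidate: 26.8 / 26 = 1.0 to 31.5 / 26 = 1.2.

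**Noise entering the model.** If none of the 26 is related to cure, 26 × 0.20 = 5.2 are expected to pass. The chance that at least one passes, if independent, is 1 − 0.80^26 = 99.7%. With the arm as a further term there are about 6.2 terms, so 26.8 / 6.2 = 4.3 to 31.5 / 6.2 = 5.1 failures per term, or 58.3 / 6.2 = 9.4 in the highest case.

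**Simulating the two-step rule.** Each row below is 600 simulated trials with 15% failures and a mix of binary and continuous candidates. Entry was at univariate p<0.20. A logistic model including the arm was then fitted and its Wald tests read at p<0.05.

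| Candidates | Patients | Mean entering | Median failures per term | At least one false predictor | AUC, same data / new data |
|---|---|---|---|---|---|
| 26 noise, independent | 178 | 5.2 | 4.4 | 69% | 0.74 / 0.50 |
| 26 noise, independent | 210 | 5.0 | 5.5 | 68% | 0.72 / 0.50 |
| 26 noise, correlation 0.3 | 178 | 5.2 | 4.5 | 53% | 0.71 / 0.50 |
| 26 noise, correlation 0.3 | 210 | 5.0 | 5.5 | 56% | 0.69 / 0.50 |
| 22 noise + 4 real | 178 | 7.9 | 3.0 | 64% | 0.85 / 0.70 |
| 22 noise + 4 real | 210 | 8.0 | 3.6 | 66% | 0.84 / 0.72 |
| 10 noise, independent | 178 | 2.1 | 9.0 | 34% | 0.65 / 0.50 |
| 10 noise, independent | 210 | 1.9 | 11.3 | 36% | 0.63 / 0.50 |

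Repeat runs with 26 independent noise variables give 66–71%. With 10 candidates the figure rises to 43% when likelihood-ratio tests replace Wald tests. Raising the failures to about 58 leaves these probabilities almost unchanged, because they depend mainly on how many candidates are screened.

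**The case against.** The strongest reply is that this model is not the trial's treatment comparison. Predictors of cure appear neither among the objectives nor among the secondary outcomes, and the chi-square test is separate. That stands, and it limits the consequence to the predictor results.

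The 26 candidates are also inferred. The article lists what is recorded and does not say that every item is screened. A shorter list may exist in a fuller document, and symptoms and vital signs are correlated. This stands too, and is why a range is given. Even so, 10 candidates leave a chance of about 34–43%.

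The failure count may be higher than 27–32, since any result other than cure counts as failure. At about 58 the model has roughly 9 failures per term instead of 4 or 5. That eases the overfitting but hardly changes the false-predictor rate.

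A reader might go further and infer that treatment itself must pass the screen, so that with equal drugs it would be dropped in about 80% of trials, the trial would lose its adjusted treatment effect, and an odds ratio could not be read against the 15-point margin. The article does not support this. It neither subjects the arm to the screen nor exempts it, its phrase about adjusting for the factors of the study may mean that the arm stays in, and it gives this model no role in judging non-inferiority.

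**Conclusion.** The point holds for the predictor analysis. Choosing variables at p<0.20 and then testing them at p<0.05 on the same 27–32 or so failures gives odds ratios, p-values and intervals that are over-optimistic. If about 26 variables are candidates, about 5 noise variables enter and the chance of at least one false predictor is about 53–71%; with 10 candidates it is about 34–43%. A false predictor is therefore more likely than not under the longer list, but not certain under either.

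These figures assume 85% cure in both arms, losses of up to 15%, and candidates mostly or wholly unrelated to cure. The primary chi-square comparison and the sample size of 210 are untouched, so the point is modest in weight, though cheap to correct.

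**What to change.** Remove the p<0.20 screen. In its place, name before unblinding a short list of baseline variables that are already collected, sized to the expected number of failures, and state that treatment arm is always in the model. The exact number is a judgement. With three named covariates and no screen, the nominal chance of any false predictor is 1 − 0.95³ = 14%.

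If the investigators want a wider search, label it exploratory and report it without p<0.05 claims. Penalised regression is one suitable method, but is not essential.

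Optionally, add a covariate-adjusted risk difference with its 95% confidence interval as a supportive analysis.

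The cost is wording only, with no new data, visits or patients. The downside is that a few covariates must be chosen in advance and fewer predictors can be claimed.
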